### **Premature termination of the study**

The study will terminate prematurely if fMRI-neurofeedback does harm to the population of interest.

## 7. Safety Reporting

### Section 10 WMO event

In accordance to section 10, subsection 1, of the WMO, the investigator will inform the subjects and the reviewing accredited METC if anything occurs, when the disadvantages of participation may be significantly greater than was foreseen in the research proposal. The study will be suspended pending further review by the accredited METC, except in so far, as suspension would jeopardize the subjects' health. The investigator will take care that all subjects are kept informed.

### Adverse events

Adverse events are defined as any undesirable experience occurring to a subject during a clinical trial, whether or not considered related to the intervention. An adverse event can therefore be any unfavorable and unintended sign, symptom, or disease temporally associated with the intervention. All adverse events reported spontaneously by the subject or observed by the investigator or his staff will be recorded. Pre-existing complaints or symptoms that increased in severity or frequency during the treatment period will be recorded as well. For each adverse event the relationship to the intervention as judged by the investigator, will be recorded. If a subject discontinued the trial because of an adverse event this will be noted.

The FCDC has the following procedure for experiments involving healthy subjects:

1. If the researcher discovers accidentally an anomalous region in the brain the only action he/she should take is to ask Prof. dr. [name] (neurologist) to look at the images. In this stage the subject is not informed about the finding.
2. Prof. dr. [name] will examine the images. He may contact a radiologist for a second opinion.
3. Prof. dr. [name] will inform the researcher about the medical relevance of the finding.
4. In case the finding represents a norm variant without any pathology the subject will not be informed.
5. In all other cases the subject will be informed by the principal investigator Prof. dr. [name]. He will contact the participant by phone and invite him/her for an

appointment. He will advise the subject to contact his/her family doctor for further medical examination. The participant will also be informed by a standard letter to the subject, signed by the principal investigator. A copy of the letter is also sent to the family doctor of the subject.

**Serious adverse events**

The occurrence of an adverse experience that is fatal, life-threatening, disabling or requires in-patient hospitalization or causes congenital anomaly will be described as "serious" adverse event and would be notified in writing to the Commissie Mensgebonden Onderzoek Regio Arnhem Nijmegen.

All adverse events will be followed until they have abated, or until a stable situation has been reached. Depending on the event, follow up may require additional tests or medical procedures as indicated, and/or referral to the general physician or a medical specialist.

## 8. Statistical Analysis

**Related to primary objective (1):** Investigate whether fMRI-neurofeedback training reduces ADHD symptoms.

For the ADHD symptom score, the sustained attention measures, the working memory measures, and the fMRI resting state anterior cingulate cortex connectivity several independent 2 x 2- way ANCOVAs (one per outcome measure) will be conducted (two-tailed, significance level is set at 5%) with session (pre-vs. post-treatment) as within-subjects factor, group (fMRI-neurofeedback vs. control neurofeedback) as between-subjects factor, and age, sex and IQ as covariates.

For the cognitive interference measures, and the fMRI anterior cingulate cortex activation level/ connectivity during MSIT several independent 6 x 2- way ANCOVA (one per outcome measure) will be conducted (two-tailed, significance level is set at 5%) with session (number of training session) as within-subjects factor, group (fMRI-neurofeedback vs. control neurofeedback) as between-subjects factor, and age, sex and IQ as covariates.

The influence of current state of motivation on training success will be calculated by computing non-parametric Spearman's rank correlations within each individual patient.

The mental strategies used will be scored and their influence on training success will be evaluated by computing non-parametric Spearman's rank correlations within each individual patient.

**Related to secondary objective (2):** Investigate if the abnormal activation levels in ADHD patients play a causal role in ADHD pathophysiology.

To estimate the influence of the neurofeedback training on the symptoms a measure of change in activation level during the neurofeedback training/ the transfer blocks at the end of the training will be developed. This measure (sessions x subjects) will be correlated with the performance on the MSIT task in the subsequent session within and across the two groups (fMRI-neurofeedback and control neurofeedback).

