### Objectives:

- (1) Primary objective: investigating whether the modulation of the ACC activation level through fMRI-neurofeedback training reduces ADHD symptoms and improves cognitive functioning.
- (2) Secondary objective: investigating if abnormal activation levels of the ACC in ADHD patients play a causal role in ADHD pathophysiology.

**Study design:** Randomized controlled treatment study with blinding of participants.

**Study population:** 20 subjects with ADHD (age > 18, IQ > 100).

**Intervention:** 10 subjects with ADHD receive 6 sessions with fMRI-neurofeedback from the dorsal anterior cingulate cortex, and 10 subjects with ADHD receive 6 sessions with fMRI-neurofeedback from a control region.

**Main study parameter:** ADHD-DSM-IV rating scale (rated blindly).

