### 3. Study Design

This study is a randomized controlled trial (RTC) with blinding of the participants and blinding of all raters. ADHD adults will be blindly allocated to one of the following two groups by a restricted randomization technique (see recruitment section):

1. fMRI-neurofeedback training, feedback from dorsal anterior cingulate cortex (n=10)
2. fMRI-neurofeedback training, feedback from control brain region (n=10)

Each group will receive the same screening, pre- and post-assessment and 6 fMRI-neurofeedback training sessions. The duration of each fMRI-neurofeedback training session will be approximately 75 minutes. The frequency will be weekly sessions. The duration of the experiment for each participant from the selection until the last session will be approximately 9 weeks.

The control group will receive exactly the same as the fMRI-neurofeedback group, except for the feedback. The control group will receive feedback from a control brain region, which will be selected such that it is activated by different tasks than the dorsal anterior cingulate cortex. This selection will be made based on literature research, previous data, and data from an ongoing pilot experiment.

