- The SA-DOTS (~15 minutes) is the so-called continuous performance task from the ANT, a computerized neuropsychological test battery (De Sonneville, 1999). During the SA-DOTS task the subject is presented random spatial dot patterns with 3-5 dots. The subject needs to press yes for a 4 dot pattern and no for a 3, or 5 dot pattern. Premature responses, false alarms, misses, the reaction time and the standard deviation of the reaction time are indicators of

the ability to maintain attention over time. The test-retest reliability of the SADDOTS is excellent (0.93 – 0.97, personal correspondence with [name]), which makes the test suited for measuring differences in the ability to sustain attention before and after the fMRI-neurofeedback training.

- During the SART (~10 minutes) single digits are presented at a rate of just over one per second. Participants are told to press a button to every number, except if that number is 3. As the task is repetitive and apparently easy, it requires participants to maintain attention.

Another neuropsychological function that has been implicated in the ADHD is working memory. Differences to healthy participants have been found for verbal as well as spatial working memory, meta-analytic findings show an effect size of 0.41 to 0.51 for ADHD versus non-ADHD (Willcutt, Doyle, Nigg, Faraone, & Pennington, 2005). Additionally, working memory capacity has been linked to successful learning during neurofeedback trainings (Hammer et al., 2012). We will thus assess verbal working memory with the Digit Span subtest of the WAIS-III-NL and visuo-spatial working memory using a visuo-spatial Nback task.

- During the Digit Span (~10 minutes) test a sequence of digits is presented orally. The digit span is then measured by forward- and reverse-order (backward) recall of the digit sequences. Backward recall is interpreted as a measure of working memory. In the standard digit span test, the sequences are presented with increasing length and testing ceases as soon as the participant makes two consecutive errors. We will use a slightly different procedure, which was developed recently: all possible trials are presented and a mean score across all trials is calculated (Woods et al., 2011). Test-retest reliability for this procedure has been shown to be very good (0.83 for backward span)(Woods et al., 2011).

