After this the fMRI training session (~50 minutes total) will start. Each training session consists of three parts: a) localizer task (~10 minutes), b) anatomical scan (~8 minutes), and c) neurofeedback training (~30 minutes). Only during the sixth and last training session there will be an additional resting-state fMRI scan (~8 minutes) at the end of the session (see above).

In this study the designated feedback region will be defined individually at the beginning of each training. At the beginning of the session subjects will thus be asked to perform the Multi-Source Interference Task (MSIT) as the localizer task. The individual fMRI data collected during performance of localizer task will be analyzed immediately using fMRI online analysis software (TurboBrainVoyager 3.0, <http://www.brainvoyager.com/products/turbobrainvoyager.html>). The general procedure and safety precautions are the same as during the resting-state fMRI (see above). Visual stimuli will be presented on a screen that the participant will be able to see by means of a mirror attached to the head coil of the MR scanner.

The MSIT is chosen as the localizer task because subjects will already be acquainted with the task, as they have performed it during neuropsychological testing (see description above). It is also known that this task robustly and reliably activates the dorsal anterior cingulate cortex, also across sessions (Bush & Shin, 2006; Bush et al., 2008). Finally, this task has been successfully used in an ADHD patient group to localize dorsal anterior cingulate cortex (Bush et al., 2008).

After localizer task and the anatomical scan the fMRI-neurofeedback training will start (see description in section 5. treatment). The fMRI setup during the training will be the same as during the localizer task.

After each training subjects will be asked to fill in a short questionnaire (~10 minutes) on the strategies that they used during this training (Sorger, 2010). Participants will also be encouraged to practise and think about the mental strategies at home in-between the training sessions. Training sessions will take place once a week.

One week after the last training session the **post-training session** (~75 minutes) will take place. All the neuropsychological tests from the pre-training session will be repeated (SA-DOTS, SART, Digit Span, Nback-task, MSIT-task, see above), as well as the assessment of ADHD symptoms performed during the screening (see above).

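### The treatment test for the ADHD score compares mean change and omits the collected baseline score as a covariate: a modest loss of efficiency at moderate pre-post correlation, not a bias

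*Protocol*

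**What the plan says.** The protocol's Summary names the main study parameter as the "ADHD-DSM-IV rating scale (rated blindly"). Section 3 allocates 10 patients to each arm.

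Section 8 tests each pre/post outcome, two-sided at 5%, in its own 2 x 2 model "with session (pre-vs. post-treatment) as within-subjects factor, group (fMRI-neurofeedback vs. control neurofeedback) as between-subjects factor", "and age, sex and IQ as covariates". The pre-treatment score enters as one level of the within-subject factor. It is not a covariate, so the term ANCOVA refers here only to age, sex and IQ.

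The baseline is available. Section 6 schedules the ADHD rating scale at screening, and the post-training visit repeats the cognitive tests "as well as the assessment of ADHD symptoms performed during the screening (see above"). Section 4 also uses the ADHD score, split into high and low, as a minimisation factor.

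The protocol gives no pre-post correlation, SD, target effect or power for the ADHD score. For two cognitive tests it gives reliabilities. On Digit Span it says: "Test-retest reliability for this procedure has been shown to be very good (0.83 for backward span"). For SA-DOTS it reports 0.93 to 0.97.

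**The concern.** A 2 x 2 session-by-group model has three effects, and only one of them is a randomised comparison of treatments. The session main effect pools both arms, so practice or expectancy would move it even if the feedback region made no difference. The group main effect averages pre and post scores and so halves any treatment effect. That leaves the session-by-group interaction, which with two time points is the difference between arms in mean change.

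A change score gives the baseline a fixed weight of one, whatever its actual relation to the post score. At moderate correlation that weight is too large, and baseline noise passes into the estimate. A regression on baseline estimates the weight instead. With 20 patients, precision on the main outcome is scarce, and the baseline measurement has already been made.

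**Working it through.** **Inputs from the protocol.** 10 per arm (Section 3); two-sided 5%; age, sex and IQ as covariates (Section 8). There is no stated power or sample-size figure to reproduce.

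**Assumptions.** Equal pre and post SDs, set to 1; rho varied because the protocol does not give it; a treatment effect of 1 SD for the power figures.

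**Step 1: the interaction is a change-score test.** In a simulated data set with 10 per arm and no covariates, the interaction F was 1.3106 and the squared t statistic for the change scores was also 1.3106.

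**Step 2: large-sample variance per patient.**
- Change score: 2(1 − rho).
- Post score adjusted for baseline: 1 − rho².
- Ratio, adjusted to change: (1 + rho)/2. The reduction is therefore (1 − rho)/2: 30%, 25%, 20% and 15% at rho 0.4, 0.5, 0.6 and 0.7.

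**Step 3: the cost of one more covariate at N = 20.** The planned model has 20 − 5 = 15 residual df (intercept, group, age, sex, IQ). Adding baseline leaves 14. Chance covariate imbalance also inflates the variance of the group effect. For p roughly normal covariates the expected factor is (N − 3)/(N − 3 − p), which is 17/14 with three and 17/13 with four. Adding baseline therefore multiplies the variance by 14/13 = 1.077, and the net ratio is 1.077 × (1 + rho)/2:
- rho 0.4: 1.077 × 0.70 = 0.754, a 25% reduction.
- rho 0.5: 1.077 × 0.75 = 0.808, 19%.
- rho 0.6: 1.077 × 0.80 = 0.862, 14%.
- rho 0.7: 1.077 × 0.85 = 0.915, 8%.
- rho 0.8: 1.077 × 0.90 = 0.969, 3%.
- rho 0.9: 1.077 × 0.95 = 1.023, a 2% increase.

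Break-even is at rho = 2 × 13/14 − 1 = 0.86.

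**Step 4: simulation at 10 per arm.** 10,000 runs per rho, age, sex and IQ in both models, effect 1 SD. In the balanced columns, high and low baseline scores are split evenly between arms.

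| rho | Variance cut, not balanced | Power, planned → adjusted | Variance cut, balanced | Power, planned → adjusted |
|---|---|---|---|---|
| 0.4 | 24.7% | 0.417 → 0.516 | 14.6% | 0.408 → 0.537 |
| 0.5 | 20.1% | 0.484 → 0.567 | 10.5% | 0.474 → 0.576 |
| 0.6 | 13.3% | 0.568 → 0.630 | 7.4% | 0.571 → 0.650 |
| 0.7 | 8.7% | 0.693 → 0.726 | 3.9% | 0.696 → 0.738 |
| 0.8 | 4.8% | 0.848 → 0.853 | 1.0% | 0.860 → 0.877 |
| 0.9 | −2.0% | 0.985 → 0.979 | −0.6% | 0.986 → 0.985 |

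The unbalanced column agrees with Step 3; repeat simulations move the entries by a point or two. Across rho 0.4 to 0.7 the power gain runs from 3 points (0.693 to 0.726) to 13 points (0.408 to 0.537). With balance, power gains more than the variance cut suggests, because the planned model's standard error takes no credit for the balance. Its mean 95% interval narrows on adjustment from 2.29 to 1.93 SD at rho 0.4 (0.36/2.29 = 16%) and from 1.61 to 1.51 at rho 0.7 (0.10/1.61 = 6%).

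**Step 5: bias.** With no true effect and no balancing, rejection rates, planned then adjusted, were 5.1% and 5.1% at rho 0.4, and 4.8% and 5.0% at rho 0.7.

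**Step 6: the cognitive tests.** If the quoted reliabilities applied as pre-post correlations, the Step 3 ratio would be 1.077 × 0.915 = 0.985 for Digit Span (0.83), and 1.077 × 0.965 = 1.039 to 1.077 × 0.985 = 1.061 for SA-DOTS (0.93 to 0.97). That is no useful gain for the first and a small loss for the second.

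**The case against.** The planned model is standard and unbiased, and the size of any gain depends on a correlation that the protocol never states. Both points stand. A reader might infer four stronger things that the documents do not support.

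- **That the plan discards a fixed 15% to 30% of precision.** Those are large-sample variance figures for an assumed rho of 0.7 to 0.4. At 20 patients the gain is smaller, and it shrinks further if minimisation balances the baseline.
- **That baseline adjustment can never do worse.** This holds only in large samples. With this trial's size and covariates the advantage is gone by rho of about 0.86.
- **That the result would be biased, or inflated by regression to the mean.** Error rates were about 5% for both models. The eligibility criteria set no rating-scale cut-off, and Section 6 also places a fuller symptom assessment in the pre-training session, so the size of any regression to the mean is unknown. It would in any case affect the pooled session effect rather than create a false difference between arms on average.
- **That failing to name the deciding effect is a separate error.** Section 2 asks for a specific effect and Section 3 builds a control arm, so the interaction is the evident test. An explicit label could sit in an analysis plan.

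A further objection is that a fuller adjustment, adding every minimisation factor, would be costly. This also stands. Dose at three levels (2 df) and high/low ADHD score (1 df), on top of continuous baseline and age, sex and IQ, spend four df and leave 11. Simulated power for 1 SD, planned against that model, was 0.475 against 0.483 at rho 0.5, 0.574 against 0.542 at 0.6, and 0.696 against 0.636 at 0.7. The gain vanishes or reverses. Sections 4 and 6 also disagree on the balancing factors: dose and ADHD score in one, ADHD score and IQ in the other.

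**Conclusion.** The point holds as a matter of efficiency for the ADHD score. The protocol itself fixes the model, so this is not a detail left to an analysis plan. With rho between 0.4 and 0.7 and equal SDs, both assumed, adding the baseline cuts the variance by roughly 10% to 25%, or roughly 5% to 15% if high and low baseline scores are balanced between arms. Power for an assumed 1 SD effect rises by about 3 to 13 points. Above that range there is little or nothing to gain. The change is worth making because the baseline exists and the possible loss at high rho is very small. It does not put the validity of the planned test in doubt, and no gain should be claimed for the highly reliable cognitive tests.

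**What to change.** In Section 8, for the ADHD score only, replace the 2 x 2 model with: post score = group + baseline ADHD score (continuous) + age + sex + IQ. State that the group coefficient, with its 95% confidence interval, is the deciding test, and that the pooled session effect is descriptive. Do not add the high/low ADHD level as well, since it is a dichotomy of the score already in the model.

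Cost: one residual degree of freedom (15 to 14) and the wording of Section 8. No new measurement is needed.

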#### fMRI-neurofeedback training sessions

- Current Motivation according to QCM
- Cognitive interference score according to MSIT
- Anterior cingulate cortex activation level during MSIT/ neurofeedback training
- Mental strategies used during neurofeedback task

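### The only MSIT interference score taken after all six trainings enters no planned between-group test

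*Protocol*

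**What the plan says.** Section 6 of the protocol (Overview Performed Measurements) includes MSIT in the pre-training neuropsychological testing. In the training sessions it serves as the localizer: "At the beginning of the session subjects will thus be asked to perform the Multi-Source Interference Task (MSIT) as the localizer task". The same section and section 5 place the feedback after the localizer and the anatomical scan. For the visit one week after the last training, section 6 states: "All the neuropsychological tests from the pre-training session will be repeated (SA-DOTS, SART, Digit Span, Nback-task, MSIT-task, see above".

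The Summary Measurements in section 6 do not follow this. The pre/post list has the symptom score, sustained attention, working memory and resting-state connectivity, but no interference score. "Cognitive interference score according to MSIT" appears only in the list for the training sessions.

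Section 8 follows the summary lists. Symptoms, sustained attention, working memory and resting-state connectivity get a 2 x 2 ANCOVA with pre versus post as the within-subject factor. Interference is handled differently: "For the cognitive interference measures, and the fMRI anterior cingulate cortex activation level/ connectivity during MSIT several independent 6 x 2- way ANCOVA", "with session (number of training session) as within-subjects factor". Both models carry "age, sex and IQ as covariates". Section 3 gives the arm size: "fMRI-neurofeedback training, feedback from dorsal anterior cingulate cortex (n=10"), with the same number in the control arm.

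**The concern.** Improved cognitive functioning is part of the primary objective (section 2). MSIT is the task that the protocol links most directly to the trained region: it is used to localise the dorsal anterior cingulate cortex. One would expect the group comparison of interference to include a measurement taken after the whole course.

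Such a measurement is collected. It is omitted from the pre/post list and is not a level of the stated model. The other four tests repeated at that visit do get a pre/post group comparison. In a trial of 20 patients, the planned interference result would describe at most five of the six trainings, and the measurement that describes all six would stand outside the comparison.

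**Working it through.** **1. What each MSIT administration follows**

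| MSIT administration | Trainings completed | In the section 8 group test? |
|---|---|---|
| Pre-training visit | 0 | no |
| Session 1, start | 0 | yes |
| Session 2, start | 1 | yes |
| Session 3, start | 2 | yes |
| Session 4, start | 3 | yes |
| Session 5, start | 4 | yes |
| Session 6, start | 5 | yes |
| Post-training visit | 6 | no |

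The last analysed run reflects 5/6 = 83% of the course. Two of the eight administrations, including the only one after training 6, are outside the between-group model.

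**2. What this costs in power**

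The protocol states no power, effect size or within-patient correlation, so there is no figure of its own to reproduce. Inputs:
- From the protocol: n = 10 per arm, six sessions, two-sided 5% level.
- Assumed: group difference d = 1.0 SD after six trainings, equal correlation ρ of 0.5 or 0.7 between any two occasions, complete data. The group-by-session interaction is taken as the treatment test.

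Power comes from the noncentral F distribution, shown without covariates. Age, sex and IQ take three degrees of freedom per patient-level error term and lower each figure by about one point.

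Formulas, with δ_k the group difference at run k:
- Six-run interaction: λ = (n/2) Σ(δ_k − mean δ)² / (1 − ρ), df 5 and 5 × 18 = 90.
- Pre/post change: λ = (n/2) d² / [2(1 − ρ)], df 1 and 18.
- Post adjusted for pre: λ = (n/2) d² / (1 − ρ²), df 1 and 17.

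*Linear growth.* δ = 0, 1/6, …, 5/6; the sum of squares about the mean is 17.5/36 = 0.486.
- Six-run interaction: λ = 5 × 0.486/(1 − ρ) = 4.86 and 8.10; power 33% and 54%.
- Pre/post change: λ = 5/[2(1 − ρ)] = 5.00 and 8.33; power 56% and 78%.
- Post adjusted for pre: λ = 5/0.75 = 6.67 and 5/0.51 = 9.80; power 68% and 84%.

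*Immediate full effect after training 1.* δ = 0, 1, 1, 1, 1, 1; the sum of squares is 30/36 = 0.833.
- Six-run interaction: λ = 8.33 and 13.89; power 56% and 81%.
- If the effect persists, the two pre/post tests keep the figures above.

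*Effect that appears only after training 6.* All six δ are 0, so the six-run test rejects at its 5% level only. The pre/post tests keep the figures above.

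*Early effect that fades.* Half the effect after training 1, full after training 2, 70% left a week after training 6. For the runs, δ = 0, 0.5, 1, 1, 1, 1 and the sum of squares is 0.875.
- Six-run interaction: λ = 8.75 and 14.58; power 58% and 83%.
- Post adjusted for pre: λ = 5 × 0.49/0.75 = 3.27 and 5 × 0.49/0.51 = 4.80; power 40% and 54%.

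The ranking of the tests thus depends on the shape of the effect. The missing level after training 6 does not.

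**The case against.** The strongest defence is that the six-session model is a legitimate way to follow learning over time, and it has substance.

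- Run 1 precedes all feedback, so the model contains its own baseline. Having that baseline as a level of the within-subject factor is not an error; the protocol's 2 x 2 models treat the pre-training score in the same way.
- The interaction test is not inferior in general. For an immediate effect it about equals pre/post change, and for an effect that fades within a week it does better than the adjusted post score. A linear contrast over the six runs is also a trade-off: under linear growth it has about 55% and 77% power against 33% and 54% for the interaction, but under an immediate effect 43% and 64% against 56% and 81%.
- The quoted sentence also covers cingulate activation and connectivity during MSIT. No scanner MSIT is planned before or after training, so for those outcomes the six sessions are all the data there are.
- The extra MSIT scores are not without any purpose. The pre-training run familiarises patients with the localizer task. Section 2 names all cognitive tasks as possible moderators. The secondary correlation with MSIT performance in the subsequent session could take in the post-training score for session 6, although the text does not say so.

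All of this stands, and it limits the point. None of it supplies a between-group comparison of interference after the full course, and none explains why a test repeated at the post-training visit is missing from the pre/post list.

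**Conclusion.** The point holds for the behavioural interference score. Section 6 collects it before training and after all six trainings, while the Summary Measurements and section 8 confine its group comparison to runs that follow 0 to 5 trainings. These places need to be reconciled. Under assumed linear growth to 1.0 SD, using the pre- and post-training scores would raise power from about 33-54% to 56-78% (change) or 68-84% (adjusted). Under an immediate effect there is little or no gain over pre/post change. These figures rest on the assumed effect size, correlation and shape; the absence of a level after training 6 rests on the text alone.

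Stronger readings that a reader might infer are not supported:
- That training 6 is never evaluated. Symptoms, sustained attention and working memory are measured a week after it, and resting-state connectivity at the end of session 6. The main study parameter, the ADHD rating scale, is unaffected.
- That the planned test is the weakest use of the data. This depends on the shape of the effect, which the protocol does not state.
- That the 6 x 2 test has an inflated type I error or loses patients who miss a session. Section 8 does not say that a sphericity correction is omitted or that incomplete cases are dropped, and both are matters for the statistical analysis plan.

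**What to change.** 1. In section 6, Summary Measurements, add the behavioural MSIT interference score to the pre/post list, so that it agrees with the description of the post-training visit.
2. In section 8, make the pre- versus post-training group comparison of that score the test of the full course, preferably as the post-training score adjusted for the pre-training score. The other cognitive outcomes use a pre/post within-subject factor instead. That form would also close the gap, with the lower power shown above.
3. Keep the six-session analysis to describe the time course of interference and for in-scanner cingulate activation and connectivity. State there that run k follows k − 1 trainings. A linear contrast is not required.
4. State whether the post-training MSIT counts as the subsequent session for training 6 in the secondary correlation.

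The cost is wording; no visit, scan or patient is added. There are two small downsides: one more stated test, and a post-training score taken a week after training 6, which could miss an effect that fades.
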